**(2)**

In these equations, 1–α denotes the significance level, *1–β* represents the statistical power, *Z_1−α_* and *Z_1−β_* are critical values derived from the Z-table, *σ* refers to the SD of the 2 groups, *δ* indicates the mean difference between groups, and *Δ* stands for the superiority margin.

According to published literature, the mean number of intraoperative fluoroscopies in screw fixation for FNFs is approximately 32.2 times [26], while the use of a navigation system is expected to significantly reduce fluoroscopy frequency. On the basis of preliminary pilot data and the experience with navigated procedures at our institution, the mean (SD) number of fluoroscopy images for the control group (nonnavigated) is 32.2 (SD 5.2), and that for the experimental group (navigated) is 15.2 (SD 3.7). The superiority margin was set at 15.4, with a 1-sided significance level of .025 and a statistical power of 0.8.

With a 1:1 allocation ratio between the 2 groups, the sample size calculation was performed using the aforementioned formula and PASS (version 15.0; NCSS LLC) software. Considering patient recruitment feasibility, each group required 126 participants, yielding a total of 252 subjects. After accounting for a 15% dropout rate and distribution across multiple centers, the final sample size was set at 150 (50%) per group, resulting in a total of 300 participants.

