### Randomization and Blinding

This is a single-blind trial in which patients and outcome assessors will be blinded to treatment allocation, while operating surgeons cannot be blinded because of the distinct intraoperative workflows associated with the navigation system and the freehand technique. Patients will remain blinded to their group assignment throughout the surgical procedure and the entire 12-month follow-up period, with the specific technique disclosed only after completion of all outcome assessments unless early unblinding is required for safety reasons. Radiographic assessors and functional outcome assessors will be blinded to group allocation, as all imaging studies and clinical assessments will be coded with unique participant identifiers and conducted without access to treatment assignment records. The primary statistical analyst will remain blinded until the final database is locked and all predefined analyses are completed, with group codes revealed only after the statistical analysis plan has been fully executed. Emergency unblinding may be performed by the principal investigator in the event of a serious adverse event for which knowledge of the intervention is essential for patient management, and any such event will be documented and reported.

Randomization will be performed by the coordinating center using a centralized computer-generated system with permuted blocks of 4 to ensure balanced allocation across treatment groups. Assignment details will be distributed to all participating sites via sequentially numbered, sealed opaque envelopes. All surgical procedures will be performed in accordance with the assigned randomization.

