### Statistical Plan

All statistical analyses will be performed using SPSS (version 26.0; IBM Corp), R (version 4.2.0; R Foundation for Statistical Computing), and Origin 2021 (version Origin 2021; OriginLab Corp), with a 2-sided significance level of *P*<.05. For the primary outcome (fluoroscopy frequency), group comparisons will be performed using a 1-sided *t* test or a Mann-Whitney *U* test, supplemented by a linear mixed-effects model with study site as a random effect to account for center-level clustering. Continuous secondary outcomes will be analyzed using similar linear mixed-effects models with baseline covariates, while categorical outcomes will be analyzed using generalized linear mixed-effects models with study site as a random intercept. For outcomes assessed repeatedly at 1, 3, 6, and 12 months, longitudinal mixed-effects models will include fixed effects for treatment group, time, and the group-by-time interaction, along with subject-specific random intercepts and slopes nested within site. Any baseline variable with a standardized difference >0.10 will be adjusted as a covariate. The center-by-treatment interaction will be formally tested; if significant (*P*<.10), exploratory subgroup analyses stratified by site will be conducted. Predefined subgroup analyses include age, gender, Garden classification, and fracture side. Sensitivity analyses will include per-protocol and as-treated analyses.

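### Choosing covariates by a standardized difference above 0.10 lets chance imbalance, not prognosis, set the supplementary and secondary models: each baseline variable has about a 39% chance of selection

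*Protocol article*

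**What the plan says.** The Statistical Plan section of the protocol article gives one explicit criterion for choosing covariates: "Any baseline variable with a standardized difference >0.10 will be adjusted as a covariate". It does not say whether the difference is signed or absolute, which variables are candidates, or which of the preceding models the rule applies to.

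The same section sets the surrounding analyses:

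- The primary outcome, fluoroscopy count, is compared by a one-sided t test or a Mann-Whitney test. A mixed model with a random effect for site is added as a supplement.
- Continuous secondary outcomes use similar mixed models with baseline covariates, none of which is named.
- Repeated outcomes use longitudinal mixed models whose listed fixed effects are group, time and their interaction.
- Age and Garden classification appear only among the subgroup factors.

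Under Sample Size, "the final sample size was set at 150 (50%) per group, resulting in a total of 300 participants". Under Randomization and Blinding, allocation uses a "centralized computer-generated system with permuted blocks of 4 to ensure balanced allocation across treatment groups", and no stratification by a prognostic factor is mentioned.

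**The concern.** In a randomized trial, a baseline difference between arms is a chance event unless randomization failed. Its size says nothing about whether the variable predicts the outcome. A rule triggered by observed imbalance therefore selects on the wrong property. It brings in irrelevant variables that happen to differ and gives no assurance that a strong predictor enters when it happens to be balanced.

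The threshold makes this worse. If 0.10 is small relative to the sampling error of a standardized difference in a trial of this size, selection will be frequent and will carry almost no information. At stake are the stability of the adjusted models, since their content is unknown until baseline data are compared by arm, and the precision that known prognostic variables could have supplied.

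**Working it through.** **Inputs.** From Sample Size: "With a 1:1 allocation ratio between the 2 groups", 150 per arm randomized, and before allowance for dropout "each group required 126 participants, yielding a total of 252 subjects". From the Statistical Plan: the threshold of 0.10.

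**Check on the group sizes.** "The superiority margin was set at 15.4, with a 1-sided significance level of .025 and a statistical power of 0.8". The planning means are 32.2 and 15.2, with SDs 5.2 and 3.7.

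- Expected difference beyond the margin: 32.2 − 15.2 − 15.4 = 1.6.
- Common SD: √[(5.2² + 3.7²)/2] = 4.513.
- Normal approximation: n = 2(1.960 + 0.842)² × 4.513² / 1.6², which rounds up to 125 per arm. The noncentral t calculation gives 126, as stated.
- Dropout: 126/0.85 = 148.2, so 149, which the plan sets at 150.

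The group sizes reproduce and can be used below.

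**Chance of crossing the threshold.** Under valid 1:1 randomization, the standardized difference d of any baseline variable is approximately normal with mean 0 and variance 2/n, where n is the number per arm. Hence P(|d| > 0.10) = 2[1 − Φ(0.10/√(2/n))].

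| n per arm | SE of d | 0.10/SE | P(\|d\| > 0.10) |
|---|---|---|---|
| 150 | 0.1155 | 0.866 | 38.6% |
| 127.5 (15% loss) | 0.1252 | 0.798 | 42.5% |
| 126 | 0.1260 | 0.794 | 42.7% |

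Simulation at 150 per arm (40,000 replicates) gives 38.0% for a continuous variable and 38.8% to 39.8% for binary variables with prevalence 5% to 50%. Read literally as a signed difference, the rule would give half of 38.6%, about 19%, and would ignore imbalance in the other direction.

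**Number of variables selected.** The article does not say how many baseline variables are candidates. Table 2 lists demographics, vital signs, medical history, laboratory tests, Garden classification, time from injury to surgery, and screening values of the three scores. For k independent variables (an assumption), the expected number selected is 0.386k and P(at least one) = 1 − (1 − 0.386)^k.

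| k | Expected selections | P(at least one) |
|---|---|---|
| 4 | 1.5 | 86% |
| 10 | 3.9 | 99% |
| 15 | 5.8 | >99.9% |

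Correlation between variables would leave the expected number unchanged but alter the last column.

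**Consequence for inference (illustrative).** Simulated trials had 150 per arm, eight independent baseline variables of which one predicts the outcome, a true effect of 0.324 SD for power, and a two-sided 5% test (6,000 replicates, no site effect). None of these settings except the arm size comes from the article.

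| Correlation with outcome | Prognostic variable selected by the rule | Null rejection: rule / fixed in advance / unadjusted | Power: rule / fixed in advance / unadjusted |
|---|---|---|---|
| 0.3 | 39.5% | 4.8% / 5.3% / 5.1% | 0.82 / 0.84 / 0.81 |
| 0.5 | 37.6% | 3.5% / 4.6% / 4.9% | 0.85 / 0.90 / 0.80 |

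The Monte Carlo error on a 5% rate is √(0.05 × 0.95/6000) = 0.3 percentage points. At correlation 0.3 the rule's null rate is therefore indistinguishable from 5%; at 0.5 it is clearly below. The rule finds the prognostic variable no more often than it finds noise.

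**The case against.** The case for leaving the rule alone has four parts.

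- **It does not touch the main test.** This stands. A t test or Mann-Whitney test takes no covariates. A reader might infer that the trial's headline result hangs on a data-driven model; the plan does not support that, because the adjusted model for fluoroscopy count is only a supplement.
- **It is mechanical and blind to outcome.** This also stands. The rule uses baseline data only, and an absolute difference can be computed from coded groups. Under Randomization and Blinding, the primary analyst remains blinded until the predefined analyses are finished. The rule gives no opening to pick covariates by their effect on the result. A reader might also infer that ignoring the selection step makes P values too small; the simulation shows the opposite direction.
- **It may add to a fixed set.** The plan says which variables will be adjusted for, not that only those will be, and its mention of baseline covariates for secondary outcomes could refer to a separate list in an unseen analysis plan. So it cannot be asserted that age or Garden classification will be left out when balanced. The article also does not show that they predict fluoroscopy count, operative time or blood loss. What survives is that the article names no covariate on prognostic grounds, so on its face such variables may enter only by luck.
- **The loss is modest.** The fall in power from 0.90 to 0.85 belongs to an assumed correlation of 0.5; at 0.3 the difference is about 0.02. In these simulations the rule still did better than no adjustment.

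None of this defends the threshold. A separate covariate list would not cure the rule, which would still add variables to the model by chance.

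**Conclusion.** The concern holds within limits. At 150 per arm the 0.10 threshold lies below one standard error, so each baseline variable has about a 39% chance of being selected when randomization has worked, and about 43% at 126 per arm. This rests on reading the rule as an absolute difference and on the normal approximation, which simulation supports. The total of 1.5 to 5.8 chance selections further assumes 4 to 15 independent candidates.

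The effect is confined to the supplementary mixed model for the primary outcome and the models for secondary outcomes. There it means a model not fixed in advance, some loss of precision, and tests that are at worst conservative. It is not a threat to the primary test or a source of false positives, and the article does not establish that any particular predictor will be omitted. Because the rule is stated outright, it is a choice to correct rather than a detail left to a later document. The correction is worth making because it is nearly free.

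**What to change.** Delete the imbalance rule. Before unblinding, name a short list of prognostic covariates for the supplementary and secondary models, adjust for them whatever the observed balance, and keep site as the random effect already planned. Age and Garden classification, plus the screening value of a score where one is collected, are examples; the final choice should rest on the investigators' view of prognosis. Standardized differences can stay in the baseline table as description only. If the analysis plan already holds a fixed list, the article should refer to it.

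The cost is about one sentence in the protocol and the matching text in the analysis plan. Table 2 shows that the example variables are already collected, and the sample size does not change. The abstract reports that recruitment was still under way at submission and that no analysis had been done, so the list could be set without knowledge of results.

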### Ethical Considerations

#### Ethics Committee Approval

This study received initial ethics approval from the institutional review board of the coordinating center, the Chinese People’s Liberation Army General Hospital (S2024-341-01, version V1.0, dated May 1, 2024). This multicenter randomized controlled trial will be carried out only after each participating site obtains separate approval from its local ethics committee. No study procedures will begin at any site prior to written confirmation of ethics approval. The study has been prospectively registered on ClinicalTrials.gov (NCT06713018).

#### Informed Consent

Written informed consent will be obtained from every participant or a legally authorized representative before any study-related procedures are performed. All eligible patients will receive comprehensive information regarding the study purpose, procedures, potential risks and benefits, alternative treatments, and the voluntary nature of participation. Patients will be explicitly informed that refusal to participate or withdrawal at any time will not affect their subsequent medical care. Consent forms will be signed and dated by both the participant and the investigator obtaining consent. For patients with cognitive impairment who are unable to provide consent but meet the inclusion criteria, consent will be obtained from a legally authorized representative in accordance with local regulations.

#### Privacy and Confidentiality

All patient data collected during this trial will be deidentified using unique participant codes, with a separate password-protected linkage file maintained by the principal investigator at each site. Paper records will be stored in locked cabinets, and electronic data will be entered into a secure platform (National Real-World Research Platform for Orthopedics, Sports Medicine, and Rehabilitation) with role-based access control and audit trails. No individual participant data that could allow reidentification will be publicly disclosed.

#### Participant Compensation

Participants may receive direct medical benefits, including early rehabilitation guidance and priority follow-up. The navigation system is provided free of charge by the Visual MedTech Co Ltd. Routine clinical costs will be charged according to national regulations. Patients completing the full study will receive a one-time stipend of RMB 400 (RMB 1=US $0.15 as of June 15, 2026) after the final follow-up, which will be covered by the funding project. Cost associated with device-related adverse events will be covered by the sponsor according to the study’s insurance arrangements.

### Dissemination

All proprietary information and materials provided by the research project team, including manufacturing processes, foundational scientific data, medical device specifications, and unpublished findings, will be treated as strictly confidential. All individuals and entities involved in the study are subject to confidentiality obligations. Disclosure to third parties is expressly prohibited without prior written authorization from the project team. These obligations remain binding following study termination or completion. No patient or public representatives participated in the design, conduct, reporting, or dissemination of this research.

## Results

This multicenter, prospective, randomized controlled trial was initiated in June 2024. Enrollment is scheduled to be completed by October 2026, with a target sample size of 300 participants. The final 12-month follow-up is expected to be completed by October 2027. Data cleaning and database locking will be performed within 3 months thereafter, followed by analyses of the primary and secondary outcomes.

The feasibility of implementing this protocol in future larger-scale studies will be evaluated using the following metrics: (1) navigation system performance will be assessed for each procedure in the intervention group, including trajectory planning accuracy, reference array stability, first-pass guide wire success rate, and the incidence of technical failures or device deficiencies; (2) retention rates will be assessed through completion of scheduled follow-up visits, imaging protocols, and patient-reported outcome measures; and (3) the volume of intraoperative data collected—including fluoroscopy frequency, operative time, blood loss, neck-shaft angle, and guide wire placement quality—will be quantified to inform data management strategies in future investigations.

Any deviations from the approved protocol will be documented and categorized as major or minor. All deviations will be reported to the coordinating center’s institutional review board and to the ethics committees of participating sites. Moreover, the clinical value of incorporating the navigation system will be determined by comparing the primary and secondary outcomes between the 2 treatment groups after trial completion. The results of this trial will provide evidence on the viability of navigation-assisted surgery using a fluoroscopy-based, workflow-preserving system for FNF fixation.

Upon completion of the trial, the results will be submitted for publication in peer-reviewed orthopedic or surgical journals, regardless of the direction of the outcomes. The coordinating center will be responsible for drafting the primary manuscript. There are no intended restrictions on the publication of results. This trial protocol has been prospectively registered on ClinicalTrials.gov (NCT06713018), and any significant protocol amendments will be documented and publicly disclosed.

## Discussion

### Principal Findings

This multicenter, prospective, randomized controlled trial is designed to determine whether the StarNav-1 intelligent navigation system is superior to the conventional freehand technique for TCS fixation of FNF. Upon completion, we anticipate that the primary outcome will be significantly lower in the navigation-assisted group than in the freehand group. This hypothesis is informed by prior studies that have reported reductions in radiation exposure with navigation-assisted techniques [15,21,27,28]. On the basis of the existing literature, we also anticipate that secondary outcomes, including guide wire placement quality, neck-shaft angle restoration, operative time, and intraoperative blood loss, will favor the navigation group [16-18]. However, as this is a protocol for an ongoing trial, all findings remain to be empirically tested.

### Comparison to Prior Work

The anticipated findings of this trial would align with a growing body of evidence supporting navigation-assisted fixation of FNF. Gao et al [22] reported that a laser-guiding navigation system significantly reduced radiation exposure duration (35 s vs 110 s in the freehand group; *P*<.001) and shortened operative time (40-45 min vs 65-75 min; *P*=.02) [15]. Recent studies of other navigation systems have reported primary success rates ranging from approximately 93% to 99% [16]. In terms of accuracy, Schep et al [19] reported that a fluoroscopy-based navigation system achieved an accuracy of 1.17 mm, while He et al [18] reported angular errors as low as 1.08° in the coronal plane and 1.25° in the axial plane using a biplanar robotic navigation system.

The novel StarNav-1 system differs from prior navigation technologies in several aspects. Unlike optical navigation systems that rely on optical tracking and image registration, which require specialized equipment, prolonged registration times, elevated costs, and therefore have experienced limited widespread adoption, the StarNav-1 is designed to preserve the conventional surgical workflow and uses only intraoperative fluoroscopy. This distinction addresses a key gap identified in the literature, as current techniques still fall short of simultaneously meeting the requirements for procedural simplicity, high accuracy, and minimal radiation exposure..

### Strengths and Limitations

This trial has several methodological strengths. The multicenter design enhances generalizability across different hospital settings. Prospective randomization with concealed assignment minimizes selection bias. Blinded outcome assessment for patients, radiographic reviewers, and functional assessors reduces detection bias. The sample size calculation was based on published literature [27] and a prespecified superiority margin, ensuring adequate power for the primary outcome.

Several limitations should be acknowledged. First, operating surgeons cannot be blinded because of the distinct intraoperative workflows associated with the navigation system and the freehand technique, which may introduce performance bias. However, the primary outcome is an objective, quantifiable measure that minimizes the impact of this bias. Second, the 12-month follow-up period may be insufficient to detect very late complications, such as osteonecrosis of the femoral head, which can occur beyond 1 year. Finally, all participating centers are in China, and findings may not be directly generalizable to health care systems with different surgical training practices or equipment.

### Future Directions

Depending on the results of this trial, several future research directions are anticipated. If the superiority hypothesis is confirmed, a cost-effectiveness analysis will be warranted to determine whether the clinical benefits justify the additional cost of the navigation system. A cluster randomized trial or a stepped-wedge design could evaluate the impact of implementing the system at the institutional level. Subgroup analyses may identify patient populations that derive the greatest benefit. Furthermore, if the system performs well for FNF, its application to other indications could be explored in future trials. Finally, integration of artificial intelligence for automated trajectory planning or augmented reality visualization represents potential next-generation enhancements to the current fluoroscopy-based navigation platform.

## Abbreviations

FNF: femoral neck fracture
NS+TCS: navigation system–assisted three cannulated screws
TCS: three cannulated screws
